### 2.5 Outcome measures

Outcome measures will be collected pre-intervention (T0) and immediately after the 5-week intervention period (T1). The primary outcome is the effect of the intervention on objective cognitive functioning. Previous studies on non-pharmacological intervention in SCD generally included standard neuropsychological tests as cognitive outcomes to evaluate post-training changes (e.g., MMSE, ADAS-Cog). However, SCD performs normally in standard neuropsychological tests and typically exhibits both ceiling and practice effects on consecutive evaluations with traditional tasks (Campos-Magdaleno et al., 2017; De Simone et al., 2021). Thus, it is necessary to adopt more-challenging cognitive outcomes for ascertaining treatment efficacy. Novel paradigms that are sensitive enough to objectively detect the subtle cognitive decline complained by SCD have been recently proposed (De Simone et al., 2023b; Kormas et al., 2020; Markova et al., 2023). In particular, in a recent paper of our group, we demonstrated that tasks assessing specific cognitive processes (i.e., associative long-term memory, working memory binding, spatial pattern separation) significantly differentiate SCD individuals from healthy controls without SCD with good overall accuracy (De Simone et al., 2023b). In addition, these tests were significantly associated with self-perceived memory functioning. According to these results, intervention-induced changes in cognition will be assessed in this study through the following tasks: (a) Face–Name Associative Memory Exam—short form (FNAME-12; De Simone et al., 2023b; Papp et al., 2014), which evaluates long-term associative memory ability; (b) Visual Short-term Memory Binding test (Parra et al., 2019), which evaluates conjunctive binding ability; (c) Spatial pattern separation test (De Simone et al., 2023b; Holden et al., 2012), which evaluates pattern separation processes; (d) Semantic-phonemic verbal fluency discrepancy (Vaughan et al., 2018). For FNAME-12, a parallel form (i.e., alternative version using similar material) will be applied for T1 evaluation in order to reduce the effects of learning and practice.

Secondary outcomes include the evaluation of intervention-induced changes in: (a) Subjective memory functioning, using Subjective Memory Complaints Questionnaire (De Simone et al., 2023b) and Multifactorial Memory Questionnaire (Raimo et al., 2016); (b) Psychiatric symptoms, using Beck Depression Inventory (BDI; Beck et al., 1961) and State–Trait Anxiety Inventory (STAI; Spielberger, 1983); (c) Quality of Life and Health status, using Short Form-36 Health Survey (Apolone and Mosconi, 1998) and Patient Global Impression of Change—PGIC (Hurst and Bolton, 2004); (d) Whole-brain functional connectivity.

Additionally, participants will be asked to complete the following questionnaires during the post-training evaluation (T1) in order to assess the acceptance, usability, and feasibility of the proposed IVR and telemedicine-based program: Simulator Sickness Questionnaire (Kennedy et al., 1993), User Satisfaction Evaluation Questionnaire (Gil-Gómez et al., 2017), Nasa Task Load Index (Hart and Staveland, 1988), User Experience Questionnaire (Laugwitz et al., 2008) and a modified version of the System Usability Scale (Brooke, 1995; Grier et al., 2013) that also includes an open question for qualitative input about users' experience.

For further exploratory analyses, we will additionally collect measures of cognitive reserve by means of the Cognitive Reserve Index questionnaire (Nucci et al., 2012) and dementia risk factors by adapting in Italian several items of the Lifestyle for Brain Health (Schiepers et al., 2018), in order to evaluate the potential impact of underlying mechanisms on the efficacy of intervention. Data related to participants' performance on the IVR cognitive tasks (e.g., accuracy, timing), which will be collected through the telemedicine platform for each individual at-home training session, will be also considered for analyses.

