In light of the foregoing, this study aims to evaluate the effectiveness of an immersive virtual-reality (IVR) and telemedicine-based multi-component intervention, combining cognitive training and a health and lifestyle education program, on objective and subjective cognitive function, psychiatric symptoms, quality of life and brain connectivity in older adults at high-risk for cognitive decline and dementia (i.e., SCD). The primary objective is to determine whether the multi-component intervention, when compared to an active control condition, leads to significant post-intervention gains in objective cognitive functioning, and whether these gains are greater than those induced by a cognitive-only condition. The secondary objectives are: (1) to assess the transfer effect of the intervention on self-perceived cognitive functioning, psychiatric symptoms and quality of life; (2) to assess intervention-induced changes in whole-brain functional connectivity, as highlighted by resting state-fMRI images; (3) to assess user compliance with telemedicine approach combined with IVR. Exploratory objectives include: (1) investigating potential moderators of intervention efficacy (e.g., demographics, cognitive reserve, SCD severity, lifestyle and dementia risk factors); and (2) evaluating hypotheses regarding neuroimaging results and their association with behavioral data (e.g., correlation between behavioral and imaging data, association between post-training brain changes and participants' characteristics, and whether intervention-induced improvements rely on specialized brain areas or depend on compensatory responses from other regions).

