### 2.3 Sample size calculation

To estimate the appropriate sample size, the G^*^Power program was used. Considering an effect size of 0.37 obtained in a recent meta-analysis on cognitive intervention in SCD (Sheng et al., 2020), a power of 0.8 and an alpha of *p* < 0.05, we applied repeated measurements of multivariate analysis of variance (three groups: MC-I group, CO-I group, AC-I group; two measurements: pre-intervention and post-intervention) for analysis. The appropriate sample size was determined to be 74. Therefore, each of the three experimental groups requires at least 25 participants.

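### One primary outcome rests on four unranked tasks and two comparisons, while the trial is sized for a single test at 0.05 and no success rule is fixed

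*Protocol article*

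**What the plan says.** Section 2.5 states: "The primary outcome is the effect of the intervention on objective cognitive functioning". It continues that "intervention-induced changes in cognition will be assessed in this study through the following tasks" and lists (a) FNAME-12, (b) the visual short-term memory binding test, (c) the spatial pattern separation test and "d) Semantic-phonemic verbal fluency discrepancy". It does not rank the tasks, combine them, or say how many must show an effect.

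The primary objective in the Introduction has two parts. The first is whether the multi-component intervention (MC-I), against the active control (AC-I), "leads to significant post-intervention gains in objective cognitive functioning". The second is whether those gains exceed the gains in the cognitive-only arm (CO-I).

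Section 2.3 gives "a power of 0.8 and an alpha of *p* < 0.05" for three groups and two time points, with the words "we applied repeated measurements of multivariate analysis of variance", and arrives at 74 participants. Section 2.9 plans a repeated-measures ANOVA or a similar technique such as a linear mixed model for the outcome measures. It describes no joint test of the four tasks.

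**The concern.** Sections 2.3 and 2.5 do not describe the same endpoint. The sample size assumes one variable tested once. The primary outcome is a construct carried by at least four variables (some tasks may yield more than one score), and the primary objective asks two questions of each. With no rule linking them, a significant result on one task of four could be reported as meeting the primary objective, and the choice of task could be made after the data are seen. The 5% error rate would then not apply to the claim that the trial exists to make.

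Naming the primary variable is a protocol decision, because the sample size depends on it. It is not a detail that can be added later without changing the power.

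**Working it through.** **1. The plan's own figure.** Inputs from section 2.3: effect size 0.37, alpha 0.05, power 0.80, three groups, two time points. Take one group-by-time F test with noncentrality λ = N × 0.37², numerator df 2 and denominator df N − 3.
- N = 74: λ = 74 × 0.1369 = 10.13, power 0.803.
- N = 73: power 0.797.

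So 74 reproduces as the smallest N for **one** test of **one** variable at 0.05. Entering f = 0.185 with a pre–post correlation of 0.5 gives the same λ, since 0.185² × 2/(1 − 0.5) = 0.1369, and so the same N.

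**2. Four tests at 0.05 if independent.** 1 − 0.95⁴ = 0.185.

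**3. Correlated tasks.** The documents do not give the correlation between the four change scores, so it is varied. Simulation: three arms of 25, no effect in any arm, four equally correlated change scores, 72 error df, each test at two-sided 0.05, 100,000 runs per setting. Each row gives the chance of at least one qualifying result across the four tasks.

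| Qualifying result | r = 0 | r = 0.3 | r = 0.5 | r = 0.7 |
|---|---|---|---|---|
| Omnibus three-group test significant | 18.4% | 17.5% | 15.9% | 13.3% |
| MC-I vs AC-I or MC-I vs CO-I significant, either direction | 31.5% | 29.6% | 26.6% | 22.6% |
| Same, only results favouring MC-I | 16.8% | 15.3% | 13.5% | 11.3% |
| Same, favouring MC-I, and omnibus test significant on that task | 8.1% | 7.6% | 6.9% | 5.7% |
| Both comparisons favour MC-I on the same task | 1.9% | 1.9% | 1.7% | 1.5% |

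The last row holds only when all arms are equal. If MC-I and CO-I are equal and both clearly beat AC-I, the first comparison is almost always met. The rule then errs at up to about 1 − 0.975⁴ = 9.6% for independent tasks.

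**4. Power if the four tasks stay co-equal.** Bonferroni gives 0.05/4 = 0.0125 per test. With λ = 75 × 0.1369 = 10.27 and df 2 and 72, power is 0.62, against 0.81 at 0.05. Reaching 80% needs about 102 participants.

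**5. What a composite would do.** For the mean of four z-scores with pairwise correlation r, when k of the four tasks share the same effect and the rest do not move, the standardized effect relative to one task is (k/4) × √(4/(1 + 3r)).
- All four respond: 1.45 at r = 0.3, 1.26 at r = 0.5.
- Three respond: 1.09 at r = 0.3, 0.95 at r = 0.5.

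The second case is realistic. Fluency discrepancy is not among the trained processes listed in section 2.7.1.1.

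**The case against.** **No text says that one significant task is enough.** This stands. A reader might infer that the plan as written accepts any task on either comparison, and so carries a false-positive rate of up to 31%. The documents do not support that. The rule is not stated, and the Introduction joins the two comparisons with 'and', not 'or'. The 31% also counts results in which MC-I does worse than a comparator, although the objective is worded in terms of gains. Counting only results that favour MC-I roughly halves it, and requiring a significant omnibus test halves it again.

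**Section 2.3 says multivariate, so perhaps the four tasks are tested jointly.** This does not stand. The section defines that analysis only by three groups and two time points, N = 74 reproduces with one outcome variable, and section 2.9 plans no joint test.

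**The sample size does match a planned analysis.** This stands in part. The group-by-time test of section 2.3 fits the repeated-measures model of section 2.9. What does not match is the number of variables to which that test is applied.

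**A statistical analysis plan or the full protocol may correct for multiplicity, and the registry entry may name one primary measure.** Possible; neither is at hand, and the absence of a correction is not the point here. The article does state both the primary outcome and the sample size, and they disagree. A correction added later would not repair this, because power would fall to about 62% per test.

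**A composite is not clearly better.** This stands. Its gain depends on most components responding, so no increase in power should be promised.

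**Conclusion.** The point holds in a limited form. The article fixes the primary outcome as four unranked tasks and two comparisons, sizes the trial for one test at 0.05, and leaves undefined what counts as success. That follows from the text alone.

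The size depends on three assumptions that the documents do not supply: that one significant task would be taken as success, that there is no effect in any arm, and how strongly the tasks correlate. On these, the rate is about 13–18% for four omnibus tests (r = 0.7 to 0). Across both comparisons at r = 0.5 to 0 it is about 13–17% for results favouring MC-I, 27–31% in either direction, and 7–8% when results favouring MC-I also need a significant omnibus test. No single one of these figures is the trial's error rate. The defect is that the plan does not determine which of them applies.

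**What to change.** Before unblinding, declare in the protocol and the registry one primary variable, tested once at two-sided 0.05. There are two ways to do this:
- a pre-specified composite of signed z-scores, stating whether fluency discrepancy is included and which direction of it is better; or
- one named task.

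Report the remaining tasks as supportive, with Holm adjustment. Put the two comparisons of the primary objective in a fixed order, for example MC-I vs AC-I and then MC-I vs CO-I.

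This changes wording only. N = 74 and 80% power remain under the sponsor's inputs, provided the 0.37 is taken to apply to the chosen variable. That 80% belongs to the three-group test, not to either pairwise comparison.

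If all four tasks are to stay co-equal primaries, apply Holm or Bonferroni and restate the per-test power as about 62% at 75 participants (about 102 would be needed for 80%).

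Downsides: a composite says less about which process changed and gains power only if most components respond. A single task narrows the claim; FNAME-12 in particular lies close to the trained face-name exercise.

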## 2 Methods/design

### 2.1 Study design

This 5-week randomized controlled trial (RCT) use a double-blinded, three-parallel group design, guided in accordance with the Consolidated Standards of Reporting Trials (CONSORT) guidelines (Bennett, 2005). Following a screening phase to verify eligibility criteria through a comprehensive clinical and neuropsychological evaluation, and after obtaining informed consent, enrolled participants with SCD will undergo an in-person baseline assessment and a 3T MRI scan (where feasible) to collect clinical, neuropsychological, behavioral, and neuroimaging data prior to the intervention (T0). Then, using a stratified randomization method (ratio 1:1:1, taking age into account), participants will be allocated in a blinded fashion to one of the three experimental conditions:

(1) a multi-component intervention (MC-I), including SCD-tailored cognitive IVR training *plus* a health and lifestyle education program;(2) a cognitive-only intervention (CO-I), including SCD-tailored cognitive IVR training *plus* an active control for the education program;(3) an active control intervention (AC-I), including active controls for both cognitive training and education program.

The active control for the cognitive training (in the AC-I condition) involves IVR tasks mirroring the experimental training's structure but with very low cognitive demands. The active control for the education program (in both CO-I and AC-I conditions) consists of educational videos on topics unrelated to dementia and cognitive decline prevention. A detailed description of the interventions is provided in paragraph 2.7.

All three groups will receive 20 training sessions (4 sessions per week, each lasting about 30 min) over a period of 5 consecutive weeks. Participants will complete their respective interventions at home using virtual reality head-mounted displays (HMD) remotely controlled and monitored in real-time via a dedicated telemedicine platform. Prior to the intervention, all participants will receive in-person training on the use of HMD tool. Within 48 h and 1 week of completing the 5-week intervention, participants will return respectively for a post-intervention 3T MRI scan (where feasible) and an in-person evaluation, in order to collect post-training clinical, behavioral, neuropsychological and neuroimaging outcome measures (T1). A study flowchart is provided in Figure 1.

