#### 2.7.1 Multi-component intervention

Multi-component intervention (MC-I) includes both a SCD-tailored cognitive training (3 sessions/week, each lasting about 30 min) and a health and lifestyle education program (1 session/week, each lasting about 20 min), for a total of 20 sessions during a consecutive 5-week period (Figure 2).

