##### 2.7.1.1 Cognitive training

The selection of the most appropriate cognitive activities to be trained was made on the basis of empirical findings showing that individuals with SCD, while performing normally on traditional neuropsychological tests, have objective deficits in specific and more demanding cognitive processes (e.g., long-term associative memory, short-term memory binding, spatial pattern separation) when compared with healthy individuals without SCD (De Simone et al., 2023b; Kormas et al., 2020; Markova et al., 2023). For example, difficulty remembering face-name associations is one of the most commonly reported memory difficulties in SCD that underlines a subtle deterioration of associative memory processes, as demonstrated in our recent paper (De Simone et al., 2023b). As such, training to enhance memory for face-name associations could be an important priority for ecologically relevant improvement in SCD. Accordingly, our IVR cognitive intervention was developed to enhance those specific processes that have been consistently found to be impaired in SCD. In particular, two different tasks were implemented in virtual real-like scenarios of daily living situations, which target the following cognitive processes, respectively: (1) long-term associative memory (i.e., the ability to learn and remember associations between previously unrelated items), (2) working memory conjunctive and relational binding (i.e., the ability to integrate multiple features within an object representation or to associate one item to its spatial or temporal context), and (3) spatial pattern separation (i.e. the ability to differentiate partially overlapping patterns of activation in order to retrieve one pattern as separate from others that are similar).

The temporal sequence of the activity to performed in each individual session of cognitive training is represented in Figure 3 and described in detail below:

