(1) Name delayed cued-recall: participants are asked to recall the associated name; responses are provided using a virtual keyboard (Figures 7A, B). (2) Name recognition: for names not correctly recalled, participants perform a three-alternative forced-choice recognition task, selecting the correct name (target) from a novel name (distractor) and a lure (a name paired with a different face; Figure 7C). (3) Occupation Delayed Cued-Recall: participants are asked to recall the associated occupation; responses are provided by using a virtual keyboard. (4) Occupation Recognition: for occupations not correctly recalled, participants perform a three-alternative forced-choice recognition task, selecting the correct occupation (target) from a novel occupation (distractor) and a lure (an occupation paired with a different face).

5) *Final screen (about 1 min)*. The intervention concludes with a final screen. Participants are asked to rate their experience using VAS ranging from 0 (not at all) to 100 (a lot) for three questions: “*Did you experience any discomfort while using the system?,” “How mentally fatiguing were these tasks?,”* and “*How satisfied are you with your performance?.”*

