Second, IVR has been related to cybersickness, a phenomenon often experienced with immersive VR environments. It typically manifests through adverse symptoms such as nausea, dizziness, headaches, and disorientation. Nevertheless, a recent systematic review of immersive VR studies conducted with elderly individuals indicated a minimal occurrence and low symptom ratings for cybersickness (Bauer and Andringa, 2020). Anyway, this aspect will be carefully examined through the analysis of data from the Simulator Sickness Questionnaire (Kennedy et al., 1993), as well as participants' qualitative reports, to thoroughly assess the intervention's usability and feasibility. Finally, and particularly relevant for at-home unsupervised interventions, is the issue of treatment adherence. Maintaining consistent engagement can be challenging outside of a controlled clinical environment. Our telemedicine approach, which includes scheduled virtual check-ins and remote monitoring functionalities, is specifically designed to explore strategies for supporting and improving adherence in this context. By examining participation rates, completion of assigned tasks, and qualitative feedback, our research aims to shed light on how remote support can influence long-term engagement and sustainability, addressing a critical open question in the management of these types of interventions.

In summary, the results of this randomized controlled trial will provide crucial evidence regarding the effectiveness of a novel multi-component intervention, integrating cognitive training and health education delivered via immersive virtual reality and telemedicine, for individuals at high risk of cognitive decline and dementia (SCD). Given its relatively low cost and accessibility, this approach has the potential to significantly contribute to primary prevention and early cognitive rehabilitation efforts aimed at reducing dementia risk.

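### The only cybersickness-specific scale is given once, up to a week after the last headset use and with no pre-exposure value, so its result will be hard to attribute to the headset

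*Protocol article*

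**What the plan says.** Section 3 (Discussion) describes cybersickness as nausea, dizziness, headache and disorientation arising in immersive VR. It says that "this aspect will be carefully examined through the analysis of data from the Simulator Sickness Questionnaire", together with participants' qualitative reports.

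Section 2.5 fixes when the SSQ is given: "participants will be asked to complete the following questionnaires during the post-training evaluation (T1) in order to assess the acceptance, usability, and feasibility" of the programme. The SSQ is one of five instruments listed there. The open question on users' experience, attached to the usability scale, is given at the same visit.

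Section 2.1 fixes the window for that visit: "Within 48 h and 1 week of completing the 5-week intervention, participants will return respectively". The two returns named there are the MRI and the clinic assessment at which the T1 measures are taken. Because the two limits apply respectively, 48 h belongs to the MRI and 1 week to the in-person evaluation. Section 2.5 calls T1 immediate, but 1 week is the limit actually set.

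A second source of symptom data is described in section 2.7.1.1. Each cognitive session closes with a final screen that asks for a 0–100 rating of "Did you experience any discomfort while using the system". That section introduces the steps as "The temporal sequence of the activity to performed in each individual session of cognitive training", so the rating recurs every time. Section 2.7.1 gives the frequency: "SCD-tailored cognitive training (3 sessions/week, each lasting about 30 min"), over 5 weeks.

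**The concern.** The article ties these symptoms to being in the virtual environment, yet its only symptom-specific scale is completed in a clinic, possibly days after the headset was last worn. Headache and dizziness also occur in people over 55 who have never used a headset. Without a value before exposure, and with every arm using the headset, a T1 score cannot be split into headset effect and background.

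At stake is what the trial can say about how well older adults tolerate headset training at home. The article promotes this mode of delivery for its low cost and accessibility. A low SSQ score at T1 could mean that symptoms were rare, that they had passed, or that those who had them were not there to report them. The schedule does not let a reader tell these apart.

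**Working it through.** The plan gives no figure for this point. The sample size in section 2.3 has no bearing on it. The check is mainly a comparison of what is measured, when and in whom.

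**1. Number and timing of measurements per participant**

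| Measure | Scheduled | When | Source |
|---|---|---|---|
| SSQ | 1 | 0 to 7 days after the intervention ends | 2.5, 2.1 |
| SSQ before any exposure | 0 | none planned | 2.5, 2.6 |
| End-of-session discomfort rating | 3 × 5 = 15 | directly after each cognitive session | 2.7.1, 2.7.1.1 |
| Symptom rating in the education video sessions | none described for the 20 − 15 = 5 sessions | – | 2.7.1.2, 2.7.2 |

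**2. Can a headset effect be isolated?** Section 2.7 puts all three interventions in immersive VR. A comparison between arms therefore contrasts task and video content, with headset exposure common to all. Only a within-person comparison with a pre-exposure value could isolate the headset, and none is planned.

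**3. What period does the T1 score cover?** The article does not say. If it covers the moment of completion, the score is taken up to a week after exposure. If it covers the home sessions, it rests on recall over about five weeks. The first would tend to miss transient symptoms. The second adds recall error of unknown direction.

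**4. Who contributes an SSQ?** Section 2.6 ends the intervention after three consecutive missed sessions and does not say whether T1 still takes place. Section 2.1 times T1 from completion of the 5 weeks. Attendance of early stoppers is thus open.

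To show how much this could matter, let p be the true proportion with symptoms, d the proportion who miss T1, and q the proportion with symptoms among those who miss it. The proportion seen at T1 is (p − d·q)/(1 − d). The document gives none of these rates, so all values below are assumptions, with p = 20%:

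- d = 10%, q = 50%: (0.20 − 0.05)/0.90 = 16.7%
- d = 10%, q = 80%: (0.20 − 0.08)/0.90 = 13.3%
- d = 20%, q = 50%: (0.20 − 0.10)/0.80 = 12.5%
- d = 20%, q = 80%: (0.20 − 0.16)/0.80 = 5.0%
- q = p, any d: 20%, no bias

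With p = 30%, the first four cases give 27.8%, 24.4%, 25.0% and 17.5%. The effect runs from nothing to a large understatement, depending wholly on the assumed rates.

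**5. Are the session ratings assigned to this question?** Section 3 names the SSQ and qualitative reports only. Section 2.5 commits performance data from the IVR tasks to analysis, with accuracy and timing as examples. Section 2.8 gives accuracy, errors and response times as examples of platform output. None of these places mentions the discomfort rating.

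**The case against.** A reader might infer something stronger: that cybersickness is measured only once and only in completers, so that the safety result must be biased towards no symptoms. The documents do not support this, for four reasons.

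- Discomfort is rated at the end of every cognitive session, 15 times as scheduled, and ratings given before someone stops do not depend on reaching T1. Only the SSQ is a single measurement.
- Section 2.6 ends the intervention, not participation in the study. That early stoppers miss T1 is possible but not stated.
- With no recall period given, neither the direction nor the size of a bias in the SSQ can be shown.
- Sections 2.5 and 3 present the SSQ as evidence on acceptance, usability and feasibility. No safety endpoint is defined.

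All four stand, and they limit the point to what is set out here.

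A further objection is that a journal article condenses the full protocol, so analysis of the session ratings may be specified elsewhere. That is fair as far as it goes: their absence from section 3 calls for a clarification and does not prove that they will be ignored. It does not answer the timing problem. The article itself fixes T1 as the occasion for the SSQ and allows up to a week, and following that schedule yields the result described.

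Finally, the session rating is one generic item. It cannot separate nausea from, say, an uncomfortable headset fit. It therefore cannot replace the SSQ, and making it the main measure would be a matter of preference.

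**Conclusion.** The point holds in a limited form. The one cybersickness-specific scale is taken once, 0 to 7 days after the last of 20 home sessions, with no pre-exposure value, no unexposed arm and no stated reference period. The 15 scheduled ratings taken close to exposure are not tied to the question. The resulting tolerability statement cannot be clearly attributed to headset use. It is liable to understate transient symptoms, more so if early stoppers do not attend T1.

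The attribution problem follows from the design as stated. The understatement is conditional: it depends on the SSQ's reference period and on who attends T1, and the article settles neither. No numerical bias can be claimed. The consequence is confined to usability and feasibility; the primary outcome and the secondary outcomes listed in section 2.5 are not affected.

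**What to change.** 1. Give the SSQ before and directly after the headset trial in the in-person onboarding session that section 2.6 already provides. This supplies the missing pre-exposure value and one reading at exposure, although the trial is only one level and shorter than a full session.
2. Give the later SSQ as close as possible to the last headset session, or when a participant stops early, for example by remote completion. State the period it refers to. T1 can stay as the occasion for the usability and satisfaction questionnaires.
3. Report the end-of-session discomfort ratings for all randomised participants, including sessions before early stopping, as a supporting tolerability measure alongside the SSQ. First confirm that the ratings are stored and that the active control arm sees the same screen. Section 2.1 says that the control tasks mirror the training's structure, but the screen itself is not described for that arm.
4. State whether participants whose intervention is terminated are still asked to attend T1.

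The cost is a few extra minutes of questionnaire time, one remote completion and possibly a higher reported symptom rate. Section 3 says the trial is already under way. For participants past onboarding, step 1 is no longer possible, but stating the reference period and using any stored session ratings still are.
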